# TREATMENT OF SUBJECTS

## Investigational product/treatment

Prior to surgery two study areas of treatment will be marked and documented by photography. Subsequently the areas will be randomly allocated to either hydrosurgical- or conventional tangential excision.

Two punch biopsies of both intervention areas will be collected before and after excision. This leads to the total number of 4 punch biopsies per patient. Type of mesh graft and expansion will also be standardised (identical mesh enlargement and symmetric covering) to ensure an equal mesh cover of the two intervention areas. Before and after excision and biopsies, surgery and topical care will be as usual.

## Use of co-intervention (if applicable)

Not applicable

## Escape medication (if applicable)

Not applicable

# INVESTIGATIONAL PRODUCT

## Name and description of investigational product(s)

**The Versajet™ II hydrosurgery system (Smith and Nephew. St. Petersburg, FL, USA)** was CE marked in 2011 and was launched in 2012^7^. It uses a high-pressure jet of sterile normal saline to debride wounds. It is attached to a console, which is then operated by a foot pedal. Physiological saline is forced out of a narrow nozzle. This jet of pressurised normal saline functions like a knife and the hand piece allows debridement and aspiration of debris to occur simultaneously. Pressure can be adjusted to facilitate the desired depth of debridement^7^.

Figure 1. The Versajet™ hydrosurgery system

[
[figure not shown]
](http://www.google.nl/url?sa=i&rct=j&q=&esrc=s&source=images&cd=&cad=rja&uact=8&ved=0ahUKEwjq1OPZnf_OAhWODBoKHX5LBNoQjRwIBw&url=http://aghaii.persianblog.ir/post/51/&psig=AFQjCNHD-mFalGjg-_jtoC1VC6bsRxy5eQ&ust=1473405568021263) [
[figure not shown]
](https://www.google.nl/url?sa=i&rct=j&q=&esrc=s&source=images&cd=&cad=rja&uact=8&ved=0ahUKEwjXzaSDr__OAhUHfRoKHYXAACIQjRwIBw&url=https://www.youtube.com/watch?v=Tq7l6fDF4qw&psig=AFQjCNH7zFKKefknUWQ6-JYbcTDVhcIQlg&ust=1473410231718655)

**Tangential blade excision** relies on the stepwise excision of a layer of tissue using a flat blade, which used to be unguarded. The addition of a guard prevents the removal of excessive amounts of tissue, and most of these knives allow adjustment of the width of the gap between the blade and the guard. If the gap is too narrow, the instrument will glide off the burn without any debridement taking place. Tangential blade excision allows the excision of slithers of tissue until healthy tissue is reached^20^.

During surgery two **punch biopsies** will be taken at both intervention areas pre- and post-excision, using a 3 mm punch, in order to confirm depth of burn. The biopsies will be processed according to a standard protocol. The biopsy will be formalin fixed and processed into 5-μm histological slides. Sections will then be stained with haematoxylin and eosin (H&E). Wound depth, dermal preservation and debridement efficacy will be measured by digital imaging analysis per biopsy.

## Summary of findings from non-clinical studies

In patients with an indication for surgical treatment of their burns admitted in one of the three Dutch burn centres in the last 6 years approximately 40% needed surgical treatment for their burn injuries. In over 80% of the operations tangential excision was the preferred technique: hydrosurgery (Versajet) in 40% and conventional excision in 60% of the cases^8^.

## Summary of findings from clinical studies

Surgical debridement is an important step in the treatment of burn patients. Its purpose is to remove necrotic and/or infectious tissue and to prepare wounds for definitive healing.

The Versajet II™ hydrosurgery system is developed for the purpose of debriding many types of wounds, including burns prior to skin grafting. It works by producing a high-pressure jet of water across an aperture in an angled handpiece. The Venturi effect creates a vacuum that removes surface debris, which is sucked into the machine together with the irrigation fluid. The cutting and aspiration effects can be controlled by adjusting console power settings, handpiece orientation, and handpiece pressure. Tissue may theoretically be excised in a tangential manner, with maximal dermal preservation. This preservation of dermal tissue, which may have been excised by conventional means, suggests that subsequent scarring might be reduced. Conventional surgical debridement of acute burn wounds prior to skin grafting commonly consists of sharp tangential excision of non-viable burn eschar with hand-held knives. This procedure is not only associated with substantial blood loss, but also with unnecessary removal of viable dermis. During the last decade hydrosurgery has become popular in burn surgery. The clinical efficacy of the Versajet™ hydrosurgery apparatus as a burn wound debridement tool has been described in several clinical studies^12,13^ and several of these support the use of the system in children^9^. The majority of these studies have reported good clinical results with minimal adverse outcomes^5,9-13^.

There are four known prospective randomised controlled trials published in the medical literature that compared Versajet™ with conventional debridement in acute and chronic wounds^1,2,14,15^, and two of which have been undertaken in burns^1,2^. It is assumed that the clinical evidence for the Versajet system would apply also on the Versajet II system, because the manufacturer’s website cites references to studies on the Versajet system rather than any new studies on the Versajet II system^7^. Therefore, the evidence of the Versajet system is summarised.

Two prospective randomized controlled trials on the Versajet system for patients with chronic wounds have been published:

- Caputo et al. (2008) measured the debridement time with Versajet (n=19) and sharp debridement using a scalpel (n=22) in patients with lower extremity ulcers. There was significant evidence (P < 0.008) of a shorter debridement time using Versajet. They did not find a significant difference in median time to wound closure^14^
- Liu et al. (2015) reported the clinical and cost effectiveness of Versajet (n=21) in comparison to conventional debridement of chronic wounds using a scalpel (n=19). They found a significant improvement for first excision time (p 0,005) and blood loss (p 0.003), but no difference in time to wound closure or bacterial count. Also the Versajet system was calculated to be cost neutral^15^.

Several prospective randomized controlled trials on the Versajet system for patients with burns have been conducted:

*Unpublished studies:*

- Anniboletti et al. (2011) reported their experience with Versajet (n=17) vs. conventional escharectomy (n=18), including 12 children. They found a shorter healing time with an average of 7 days. There was no difference in time to debridement or healing time. This study was only presented at a conference so additional information on the study could not be found^21^.
- Esposito et al. (2009) reported their experience with Versajet (n=14) vs. conventional escharectomy (n=12), including 8 children to evaluate speed to debridement. They did not find a time difference. This study was only presented as a conference abstract^22^.

Both studies described the Versajet system to be an easier operating tool to reach the desirable dermal plane.

*Published studies:*

- Gravante et al. (2007) compared Versajet (n=42) to conventional escharectomy (n=45) in adults. They found a shorter debridement time for difficult areas such as the face, hands and genitalia. However, operating time overall was equivocal. They didn‘t find a significant difference in complete healing of the wounds, post-operative pain or contractures at 6 months^1^.
- Hyland et al. (2015) compared the Versajet system (n=30) to conventional debridement (n=31) in children (≤ 16 years). They found a histologically confirmed significant difference in the amount of viable dermal preservation between the two groups (p 0.02) with more viable tissue lost in the conventional group. They did not find a significant difference between graft take at day 10, amounts of post-operative wound infection, duration of surgery time or time to healing after grafting. There were no significant differences found between scarring at 3 or 6 months after surgery.

Although scar quality is considered to be one of the most important outcomes in burn surgery, none of these studies addressed scar quality as a primary outcome. Only Hyland et al. assessed scar quality after 3 and 6 months as a secondary outcome measure using the modified Vancouver Scar Scale. This scale is a subjective scale, only taking the observers opinion into account^23^. They didn‘t study patient perception of scars and didn’t perform any objective scar measurements. Data on long term follow-up was also unavailable which is essential as scars mature over a period of at least one year^16^.

A retrospective observational study conducted at the Burn Center of the Martini Hospital of Groningen did compare scar quality as primary long term outcome, using the observer scale of the POSAS, which is a subjective assessment tool^3^. They reported a better scar quality after hydrosurgical excision in a subgroup (age 5 years and older) of their study population. To provide stronger evidence whether hydrosurgery results in a superior scar quality, a prospective study is needed to confirm the promising results of this retrospective study.

## Summary of known and potential risks and benefits

**Tangential blade excision**: Since the blade is long, this technique will only work on a convex curved surface. Such convexity can be found in many, but not all parts of the body. Areas such as those around the hands, malleoli and the axilla are difficult to excise in this manner. These knives allow the excision of slithers of tissue until healthy tissue is reached. This technique has the advantage of being fast and can lead to the removal of too much tissue although that has no adverse effect on the skin graft. Another potential problem with tangential blade excision is that at the periphery of the excision there is inevitably some ‘shelving’ of the excision, as the depth of excision slopes from zero at the very edge to deeper once the limit of the guard is reached. As split thickness skin grafts are usually of a uniform thickness, this will lead to an excess of tissue at the periphery of the wound. This can lead to a ‘stuck on’ appearance of the skin graft.^20^

**The Versajet™ hydrosurgery system (Smith and Nephew)** in expert opinion allows a more precise removal of unhealthy tissue and has the ease of blade excision but reduces the potential for excessive, unnecessary removal of healthy tissue. This technique allows the narrowest excision margin currently available, as layers of as little as 50 μm (0.05 mm) can be removed ^20^.

In paragraph 6.3 a summary of findings from clinical studies is described. The outcomes suggested mixed results.

## Description and justification of route of administration and dosage

Not applicable

## Dosages, dosage modifications and method of administration

Not applicable

## Preparation and labelling of Investigational Medicinal Product

Not applicable

## Drug accountability

Not applicable

# NON-INVESTIGATIONAL PRODUCT

Not applicable

# METHODS

## Study parameters/endpoints

### Main study parameter/endpoint

- Scar quality assessed as the total observer score of the POSAS at 12 months post-surgery scored by 2 blinded observers independently^24,25,25^

### Secondary study parameters/endpoints (if applicable)

- Dermal preservation (2 punch biopsies pre- and post-excision).
- POSAS scores: a validated questionnaire designed for subjective evaluation of

various types of scar formation^25,26^ (see paragraph 8.3)

- Global perceived change: the anchor question of the POSAS, to be able to assess the minimal clinical important change and minimal clinically important difference of the POSAS (see Statistical analysis, p.32)^18,19^
- Scar elasticity measured with the Cutometer®, a validated instrument. It measures the vertical deformation of the skin in millimetres when the skin is pulled by means of a controlled vacuum into a circular aperture^27^. (see paragraph 8.3)
- Scar colour and pigmentation measured with the Dermaspectrometer®. This is a validated instrument to measure scar colour by a narrow-band simple reflectance meter ^28^. (see paragraph 8.3)

### Other study parameters (if applicable)

- Demographics: age, sex
- Burn characteristics: % total burned body surface area (TBSA), anatomical affected site(s), date of injury, burn depth determined by an experienced burn physician and burn depth determined by a LDI-scan on date 2-5 post burn (prior to the operation), date of surgery.
- Clinical characteristics: Fitzpatrick skin type, timing to surgery, wound healing time (measured in days till 95% re-epithelization), determination of bacterial load, comorbidity, weck knife, dermatome and Versajet settings, expansion of skin graft , adverse events (blood loss, graft loss, wound infection) and need for reconstructive surgery.

## Randomisation, blinding and treatment allocation

Randomisation will be at intra-patient level. In each patient two intervention areas will be appointed, and defined A and B. The allocation of the treatment will be at random using the online randomisation program CASTOR, <https://data.castoredc.com>. In surgical treatment blinding is not possible, as the burn surgeon knows which part of the wound receives what surgical treatment. After randomisation the local principal investigator and the central trial co-ordinator will receive an email with the inclusion number and the randomisation outcome. The outcome will be displayed on the website as well, only visible for the central trial co-ordinator. Outcome assessment will be blinded as the junior investigator/research nurse who does the follow-up measurements is unaware of the technique used in areat A or area B.

In case of randomisation related difficulties the central trial co-ordinator or research coordinator can be contacted.

## Study procedures

**Peroperatively**

After receiving adequate information and when informed consent is signed two study areas of equal burn deapth are marked as area A and area B (figure 2). This must be documented by photography prior to surgery. We will take a 3 mm punch biopsy from part A and part B (figure A, dot A and B). After the biopsies we randomly allocate part A and B to hydrosurgical- or conventional excision. After-debridement we will take one more punch biopsy from both wound areas (figure 2, dot C and D), adjacent to the previous punch biopsy site in an area of confluent depth, prior to application of a split thickness skin graft. Type of mesh graft and expansion will be standardized to ensure an equal mesh cover of the two intervention areas.

Figure 2. Location of punch biopsies.

[figure not shown]

In this trial we use the smallest punch biopsy with a diameter of 3 mm, as interference is limited since a better scar quality is the aim of this study. Wound tissue is collected before and after excision in both intervention areas, which leads us to the total number of 4 punch biopsies per patient.

The stained biopsy specimens will be analysed using light microscopy. To determine the amount of dermal preservation and hence precision of debridement, the amount of viable tissue on pre- and post-debridement specimens will be recorded.

**Post-surgery and follow-up**

Patients will be assessed in both the acute phase and during the outpatient follow-up. We will record all complications during and post-surgery and the time to wound closure (95% re-epithelization). Blinded follow-up measurements will be performed at 3, 6 and 12 months post-surgery by trained research nurses and/or junior researchers. These study follow-up visits will take place in the outpatient clinic and the timing is similar to the standard follow up schedule after a burn injury in Dutch specialized burn care.

During this visit the POSAS, anchor questions (global perceived effect) of the POSAS, the Cutometer® and DermaSpectrometer® measurements will be administered and whether the patient has had reconstructive surgery. All study wounds and scars will be documented by photography before excision and 3,6 and 12 months after excision.

*Subjective scar assessment*

Patient and Observer Scar Assessment Score (POSAS)

The Patient and Observer Scar Assessment Scale (POSAS) will be used to assess the scar quality of part A and part B. This validated questionnaire enables both patient and observers to assess the same scar on six different scar characteristics, with roughly an overlap of four characteristics. The patient assesses the scar on pain, pruritus, colour, thickness, surface roughness and pliability, while the observer assesses the scar on vascularity, pigmentation, thickness, relief, pliability surface study areas A and B. Both use a numerically 10-point scale in which 1 represents a scar comparable with ‘normal skin’ while 10 represents the ‘worst scar imaginable’. Both patient and observer independently assess the same scar. The observer assessment will be performed by an experienced and trained observer, either a physician, nurse or researcher. ^23,29^

Anchor question of the POSAS

The anchor is a question regarding change in perceived scar quality in the intervening periods between two assessments and can be answered on a 5-point Likert scale. This scale has the following response options: much better/slightly better/no change/slightly worse/much worse and will be added to the POSAS used for the 6 and 12 months follow-up assessment. Another anchor question is about whether patients think that the scar of area A is better than the scar of area B or vice versa. Again, response options can be chosen on a 5-point Likert scale with the following options: much better/slightly better/no change/slightly worse/much worse.

*Objective scar assessment*

The measurements with the Cutometer® and Dermaspectrometer® have to be performed on fixed locations in order to prevent selection bias in collecting the objective data. They will be performed on 5 locations following an algorithm in which scars are divided by two lines from the widest length and width through the centre of the scar (diamond shape). The 5 points are chosen halfway between these lines and in the centre. All measurements will be done this way separately in study area A and study area B of the wound. This algorithm is used in different other studies and is illustrated in the figure 3 below ^30,31^.

[figure not shown]

Figure 3. Location of the 5 measurements

Cutometer**®** Skin Elasticity Meter 575
The Cutometer® (Courage-Khazaka electronic GmbH Cologne, Germany) is a non-invasive suction device that has been applied for the objective and quantitative measurement of skin elasticity. It measures the viscoelasticity of the skin by analysing its vertical deformation in response to negative pressure^23^. The Cutometer® provides several elasticity parameters. In case of substantial heterogeneity in individual scars, these will be measured following a standardised method, including 5 scar (figure 3) and 2 control measurements. The first option for the control measurements will always be the patients’ contralateral site. In case the contralateral site is also affected, the most comparable and unaffected spot near the scar will be used.

DermaSpectrometer

The Dermaspectrometer® (Cortex Technology ApS Hadsund, Denmark) will be used to characterize vascularity and pigmentation and thus the colour of scars/skin. This instrument’s light emitting diodes emit light at two defined wavelengths: 568 nm (green) and 655 nm (red). A photo detector measures the light reflected by the skin. It measures the absorbed and reflected light at wavelengths, respectively, in the green and the red for haemoglobin and for melanin. A melanin index and an erythema index are computed from the intensity of the absorbed and the reflected light at, respectively, 568 and 655 nm^25^. All scars will be measured following a standardised method, including 5 scar (figure 3) and 1 control measurement. The first option for the control measurement is patients contralateral side. When this is not possible the measurement must be done on an adjacent location.

To analyse the indices for erythema and melanin the absolute values of the subtraction of the scar and normal skin will be used.

In table 1 a summary of the study procedures is presented.

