Our secondary objectives are 1) To compare dermal preservation following tangential excision either performed hydrosurgically or conventionally and 2) To determine the minimal clinical important (MIC) change of the Patient and Observer Scar Assessment Scale (POSAS). The POSAS has proven to be a reliable, feasible and valid scar assessment scale. As clinimetric development is ongoing, a value for the MIC (minimal important change) is still lacking. Without a MIC, it is not possible to translate POSAS scores into clinical important and relevant differences for patients^18,19^. Especially in this study, in which the expected differences in scar quality between the two excision techniques may be subtle, a MIC value is crucial for interpreting study results. For this reason, we will conduct a clinimetric sub study alongside this RCT to determine the MIC of the POSAS. Additionally, we will determine the MCID (Minimal clinically important difference) of the POSAS at final follow up. This is the minimal difference in scar quality that patients experience as important.

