## Sample size calculation

Power calculation is based on the result obtained by Scholten et al.^3^ in their retrospective study on scar quality after hydrosurgery versus guarded knife excision.

The mean POSAS Observer Score in the hydrosurgery was 14.7 versus 16.7 in the guarded knife group 12 months post-surgery, with a pooled SD of 6.53, resulting in an effect size of 0.3. Because of the within-subject design, a correction for correlated samples was included, assuming a correlation of 0.4 between POSAS Observer Score within one patient. Given a power of 0.8 and a level of significance of 0.05 a number of 105 patients is needed. Because our primary outcome is not assessed until one year post-surgery we anticipate on a drop out of 30%, which means we will include 137 patients.

Annually approximately 750 patients are admitted to one of the three Dutch burn centres. From these patients approximately 300 will require a surgical intervention of which 240 consists of tangential excision. We expect that the majority of these patients, but at least 144 patients (60%), will be eligible for this study. From these eligible patients we expect 108 patients (75%) to give informed consent to participate in the study per year. So, we expect to be able to include 137 patients in 16 months.

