## Secondary study parameter(s)

Differences in viable dermis after excision (measured by histopathology), differences in time to wound healing (time to 95% re-epithalisation in days), scar elasticity (measured by the Cutometer®) scar vascularisation and pigmentation (measured by the DermaSpectrometer®) will be analysed using the Wilcoxon signed-rank test or paired student t-test if the data are normally distributed.

The MIC will be determined following the anchor-based MIC distribution method^32^. The anchor is a question regarding change in perceived scar quality in the intervening periods between two assessments and can be answered on a 5-point Likert scale. The MIC will be calculated in patients who slightly improved between three and six months post-surgery (longitudinal). We will determine the MCID (minimal clinical important difference) of the POSAS using the mean change method. This will happen at final follow-up (cross-sectional) at one year post-surgery. The anchor question is about whether patients think part A of the scar is better than part B or vice versa. Response options can be chosen on a 5-point Likert scale. The MCID is equivalent to the mean change in score of patients who think part A of the scar is slightly better than part B or vice versa.

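### The 12-month A-versus-B anchor reuses the answer options of the change-over-time anchor, so the group that defines the MCID can be misclassified

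*Protocol*

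**What the plan says.** Protocol section 8.3 (Anchor question of the POSAS) describes two anchors.

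- **Change over time.** The first asks how perceived scar quality changed between two assessments: "This scale has the following response options: much better/slightly better/no change/slightly worse/much worse and will be added to the POSAS used for the 6 and" (the sentence goes on to the 12-month assessment).
- **A against B.** The second compares the two study areas: "Another anchor question is about whether patients think that the scar of area A is better than the scar of area B or vice versa". Its answers are: "Again, response options can be chosen on a 5-point Likert scale with the following options: much better/slightly better/no change/slightly worse/much worse".

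Section 10.2 builds the MCID on the second anchor. On timing it says: "This will happen at final follow-up (cross-sectional) at one year post-surgery". On the definition it says: "The MCID is equivalent to the mean change in score of patients who think part A of the scar is slightly better than part B" (and likewise with the areas swapped). It describes the answers only as a 5-point Likert scale and does not restate or correct the options. Section 1 announces the same quantity: "Additionally, we will determine the MCID (Minimal clinically important difference) of the POSAS at final follow up".

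**The concern.** The five options suit the first anchor. They do not suit the second, for two reasons.

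1. **Direction.** The stem names both areas but leaves open which is the reference, and no option names an area. A patient who finds B slightly better can tick *slightly better* as naturally as one who finds A slightly better.
2. **Midpoint.** *No change* describes a course over time. A patient who sees A and B as equal has no option that says so. Both anchors are due at 12 months with the same answer words, so a patient who sees two equal, improving scars could tick *slightly better* on the comparison.

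The MCID is the mean score difference in one answer group, so patients wrongly placed in that group bias it directly. A later analysis cannot recover which area a patient meant or which question was answered. At stake is the yardstick for judging whether a difference between techniques matters to patients. An MCID that is too small makes a small difference look important.

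**Working it through.** **Inputs from the protocol.** There is no figure for the MCID, for the size of the anchor groups or for any error rate, so there is no stated result to reproduce. Three facts matter.

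- The MCID is a mean in the *slightly better* group (10.2).
- A and B are marked, at equal burn depth, before allocation (8.3): "After the biopsies we randomly allocate part A and B to hydrosurgical- or conventional excision". Treatment therefore adds no expected A–B difference among answers that have nothing to do with A versus B.
- On the POSAS a lower score is better (8.3). For a patient taken to prefer A, the signed difference is score B minus score A.

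**Formulas.** Let δ be the true mean signed difference among patients who really find one area slightly better.

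- A share f of the group means the opposite area: (1 − f)δ + f(−δ) = δ(1 − 2f).
- A share m answered about change over time, with expected difference 0: (1 − m)δ + m·0 = δ(1 − m).

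**Results** (δ, f and m are all assumed):

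| True MCID | Reversed answers, f = 10% / 20% / 30% | Change answers, m = 10% / 20% / 30% |
|---|---|---|
| 2 | 1.6 / 1.2 / 0.8 | 1.8 / 1.6 / 1.4 |
| 3 | 2.4 / 1.8 / 1.2 | 2.7 / 2.4 / 2.1 |
| 4 | 3.2 / 2.4 / 1.6 | 3.6 / 3.2 / 2.8 |

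For example, 3 × (1 − 0.4) = 1.8 and 3 × (1 − 0.2) = 2.4. For the same share, reversed answers do twice the damage.

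**Simulation of the change-answer route.** The spread was taken from section 4.4: SD 6.53 and within-patient correlation 0.4 give a paired-difference SD of 6.53 × √(2 × 0.6) = 7.15. These are Observer Score figures, used only for scale. Further assumptions:

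- The A–B difference is normal with mean 0.
- The patient's perception adds independent noise of equal SD.
- Category limits lie at ±0.4 and ±1.2 SD of perception.
- Change answers are independent of the A–B difference: 3%, 7%, 25%, 40% and 25% from *much worse* to *much better*.

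| Patients answering about change | 0% | 10% | 20% | 30% |
|---|---|---|---|---|
| Their share of the *slightly better* group | 0% | 16.2% | 30.5% | 42.7% |
| Signed mean, *slightly better* | 3.82 | 3.21 | 2.66 | 2.20 |
| Signed mean, pooled with sign-reversed *slightly worse* | 3.83 | 3.44 | 3.05 | 2.67 |
| Mean absolute difference, pooled | 5.22 | 5.26 | 5.31 | 5.37 |

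The second row agrees with the formula: 3.82 × (1 − 0.305) = 2.65. Pooling both directions softens the loss. Absolute differences do not shrink.

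**The case against.** The strongest reply has four parts.

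**The stem names both areas.** If patients take A as the subject, *slightly better* means A and *slightly worse* means B, and the item works. This is partly right: a reader might infer that the item names no area at all, but that is true only of the options. The stem's open direction is what makes the fixed reading unsafe.

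**Change answers are conjecture.** Patients have a separate question for improvement on the same form, which could reduce confusion rather than cause it. Section 8.3 describes the items, and the form is not shown. This stands as to frequency, and it is why the open direction is the clearer route to error.

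**The direction of bias depends on the analysis.** A reader might infer that the MCID must come out too small. The documents do not support that: section 10.2 does not say whether signed or absolute differences are averaged, and with absolute ones the shrinkage disappears. Absolute differences are still no remedy. In the simulation they give 5.22 against a signed 3.82 with no misclassification at all, and the average absolute difference over all patients is 5.71 (7.15 × √(2/π)). The absolute mean in the group hardly reflects what those patients noticed.

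**The consequences are limited.** The primary analysis in 10.1 does not use the MCID, no decision rule rests on it, and the secondary objectives in section 2 list only the MIC. This stands in full.

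**Conclusion.** The point holds as a defect in how a secondary item is collected. The options of the A-versus-B anchor do not fit its question, and section 10.2 relies on one of those options to define the MCID. If signed differences are averaged, the MCID is multiplied by about 1 − 2f or 1 − m. Neither share is known, so the size can only be shown as a range. The change-answer factor also assumes no systematic difference between areas by label, which marking at equal depth before random allocation supports.

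A reader might go further and note that a true MCID of 3 with m = 40% gives 1.8, below the 2.0-point difference (16.7 − 14.7) behind the sample size. That comparison should not be used. Both inputs are assumed, and the 2.0 is a difference in Observer Score (4.4: "The mean POSAS Observer Score in the hydrosurgery was 14.7 versus 16.7 in the guarded knife group 12 months post-surgery, with a pooled SD of", the SD being 6.53), whereas the anchor is the patient's opinion and 10.2 does not say which POSAS scale the MCID uses.

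The effect is confined to the MCID and to interpretation that leans on it. The primary test is unaffected, and so is the MIC, which uses the first anchor.

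**What to change.** 1. In 8.3 and on the form, give the A-versus-B anchor these options: *area A much better / area A slightly better / no difference between A and B / area B slightly better / area B much better*. Keep the change wording for the first anchor only.
2. In 10.2, state that the MCID is the mean signed difference oriented toward the area named as better: score B minus score A when A is named, and score A minus score B when B is named. Call it a difference rather than a change.
3. Flag any answers already collected with the present options and examine them in a sensitivity analysis, with and without them. Outright exclusion is not justified: the stem did name both areas, the error rate is unknown, and the loss would fall on a single answer category.

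The cost is one line on the form and in 8.3 and one sentence in 10.2, with no extra visit, item or patient. It is cheapest before 12-month visits begin; after that, the sensitivity analysis is the only added work.
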